#### 3.1. Study outcomes

##### 3.1.1. Primary outcome measure

- Number of days of post-operative recovery

##### 3.1.2. Secondary outcome measures

- Presence or absence of the tonsil related complaint
- Number of episodes of tonsillitis per year objectified by the general practitioner or ENT specialist
- Number of antibiotics courses for tonsillitis each year
- Average number of days per year of sick leave due to tonsil-related complaints
- Presence / absence of halitosis
- Presence / absence of detritus
- Pain complaints during / after the procedure
- Complications
- Patient satisfaction with regard to the procedure and reduction of complaints (using VAS)
- Time to return to work / school resumption
- Number of days of sick leave in the year after surgery (second follow-up study)
- Cost Effectiveness laser tonsillotomy vs classic tonsillectomy (second follow-up study)
- Budget Impact laser tonsillotomy vs classic tonsillectomy (second follow-up study)

## 4. Study design

### 4.1. Study-design

The study will be conducted as an unblinded multicenter randomized controlled trial. The patient will be randomized for a classic tonsillectomy or a laser tonsillotomy.

The patients will be included in the study after written informed consent.

The CO2 laser tonsillotomies will take place in a treatment room that meets the laser criteria in the outpatient intervention room of the Haga Hospital, location Sportlaan (The Netherlands). The classic tonsillectomies will be performed in the operating rooms of the participating center where the patient has been enrolled.

The number of visits by the patient to the hospital is shown in the enclosed Flow-Chart (figure 1).

[figure not shown]

## 5. Study population

### 5.1. Population

The study population will consist of men and women older than 18 years with tonsil-related complaints as described in more detail under indications.

### 5.2. Inclusion criteria

- Patients over 18 years old
- Indications:
  - Chronic / recurrent tonsillitis, > 4 tonsillitis / year (ZATT guideline, ENT association [17]) and / or
  - Halitosis and / or
  - Complaints of tonsillolithiasis and / or
  - Dysphagia and / or
  - OSAS (proven) caused by the tonsils

### 5.3. Exclusion criteria

- Troubled or uncooperative patient, at the discretion of the treating physician
- Inability to keep mouth open for long periods
  - $\leq$  5 seconds in a row
  - < 30 minutes at intervals during which the jaw can be relaxed
- High strangulation reflex
- Tonsils that are too big (Friedman IV)
- Insufficient exposure of the entire tonsil
- History of peritonsillar abscess
- Hemorrhagic diathesis / use of blood thinning medication
- Allergy to local anesthetic
- Extensive history of co-morbidity in which anesthesia is not desirable or local anesthesia is not desirable
- Immune compromised patients

## 6. Treatment specifications (intervention)

### 6.1. Treatment to be investigated

The CO2 laser tonsillotomies will be performed in the outpatient intervention room of the ENT department the Haga Hospital, location Sportlaan. The treatment room meets the criteria as formulated in the book “laserveiligheid in de gezondheidszorg (“laser safety in health care”) ([www.laserveiligheidindegezondheidszorg.nl](http://www.laserveiligheidindegezondheidszorg.nl)). Everyone present must wear safety glasses and a warning will be visible outside the room. 1000 mg of Paracetamol is given pre-operatively. The procedure is performed in a semi-reclining position. The tonsil and the superior, lateral and anterior sides of the pharyngeal arch are infiltrated with xylocaine 2% and adrenaline 1: 80,000. You will wait about 10 minutes for the anesthetic to take effect. It uses an F125 laser from Lumenis (Acupulse Surgitouch CO2 laser system) with a beam diameter of 3 mm, with a power of up to 29 watts. The tonsil is presented with a tongue depressor after which the surface of the tonsils is evaporated layer by layer in a

sweeping motion. The patient is instructed to take a deep breath before the laser is activated and to exhale slowly during the actual laser treatment. The smoke created by the evaporation is continuously extracted by a smoke suction device.

Initially, the CO2 laser tonsillotomies will only be performed in the Haga Hospital. After training ENT doctors from other hospitals, it is examined whether the CO2 laser tonsillotomies can also take place in other clinics. If this turns out to be possible, an amendment will be submitted to request permission to expand.

## 6.2. Control treatment

The classic tonsillectomy is planned in one day admission or short clinical admission in the center of inclusion, this procedure is possible in all centers participating in this study. Peroperatively, a peripheral infusion is taken. The patient is placed in the supine position in the operating room and placed under general anesthesia, after which the patient is intubated. A mouth spreader is then placed in the mouth. An Alyss clamp is applied to the superior pole of the tonsil. An incision is then made through the anterior pillar of the tonsil to visualize the underlying capsule. The incision is made close to the anterior crease and is extended through the mucosa to the base of the tonsil. The tonsil is then removed with the help of a tonsil forceps. Meshes are applied to stop bleeding. After removing the gauze after 5 minutes, the wound bed is checked to see if it is dry and bipolar electro-coagulation is carried out if necessary. The mouth spreader is removed when the wound bed is dry. After the operation, the patient is admitted to the ward.

Post-operative pain relief both procedures:

Prescription paracetamol 500mg 4dd2, use if necessary at the patient's own discretion.

Prescription diclofenac 50mg 3dd1, use if necessary for the first 3 days at the patient's discretion.

## 7. Methods

### 7.1. Primary endpoint

- Number of days post-operative recovery to resumption of daily activities

### 7.2. Secondary endpoints

- In / or absence of the tonsil-related complaint
- Number of episodes of tonsillitis per year objectified by the general practitioner or ENT specialist
- Number of antibiotic courses for tonsillitis each year
- Average number of days per year of absenteeism due to the tonsil-related complaints
- Presence / absence of halitosis
- Presence / absence of detritus
- Pain complaints during / after the procedure
- Complications
- Patient satisfaction with regard to the procedure and reduction of complaints (using VAS)
- Time to return to work / school resumption
- Number of days of sick leave in the year after surgery (second follow-up study)
- Cost Effectiveness laser tonsillotomy vs classic tonsillectomy (second follow-up study)
- Budget Impact laser tonsillotomy vs classic tonsillectomy (second follow-up study)

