## 8. Statistical analysis

### 8.1. Descriptive statistics

This study will contain different types of data. Both qualitative data and quantitative data are used. The measurements are made using four measuring scales: ordinal, nominal, interval and ratio. Which scale is used depends on the variable.

The following patient characteristics will be stored in the database which will be analyzed later:

- Date of birth
- Comorbidities
- Medication use
- Smoking / not smoking
- Head complaint (Sore throat with fever, sore throat without fever, dysphagia, detritus, halitosis, OSAS)
- Presence of other complaints (Sore throat with fever, sore throat without fever, dysphagia, detritus, halitosis, OSAS)
- Number of antibiotics used in the past year in connection with tonsil-related complaint
- Number of days of absenteeism from work / school related to tonsil-related complaints
- VAS score with regard to complaints (to be completed per complaint)
- Friedman classification (see appendix 1)

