## 8.2. Analysis

All analyzes will be performed with an intention-to-treat analysis.

A two sided p value  $<0.05$  will be considered significant for all analyses. Survival analysis will be used to compare the primary outcome of recovery time. Survival analysis will also be used to compare time to return to work and postoperative analgesic use. Secondary outcome measures on a continuous scale will be compared using unpaired T-tests or Mann-Whitney U tests, depending on the normality of data (tested using Shapiro-Wilk test). Proportions will be compared using Fisher exact tests.

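### Halitosis, detritus, tonsillitis and antibiotic outcomes carry no baseline restriction, so on the natural reading patients who never had the complaint count as free of it and absolute differences shrink

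*Protocol*

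**What the plan says.** Section 5.2 lists five indications joined so that any one suffices: recurrent tonsillitis ("Chronic / recurrent tonsillitis, > 4 tonsillitis / year (ZATT guideline, ENT association [17]) and / or"), halitosis ("Halitosis and / or"), tonsillolithiasis, dysphagia and proven OSAS.

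Sections 3.1.2 and 7.2 list among the secondary endpoints "Presence / absence of halitosis", "Presence / absence of detritus", "Number of episodes of tonsillitis per year objectified by the general practitioner or ENT specialist" and the yearly number of antibiotic courses for tonsillitis. None refers to the patient's status before surgery.

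Section 8.2 states: "All analyzes will be performed with an intention-to-treat analysis". It adds: "Proportions will be compared using Fisher exact tests". Continuous secondary outcomes get a t-test or a Mann-Whitney test, which I take to cover the yearly counts. No test is adjusted for baseline complaint or indication.

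Section 8.1 records the main complaint at baseline, and also "Presence of other complaints (Sore throat with fever, sore throat without fever, dysphagia, detritus, halitosis, OSAS". It also lists an effectiveness variable defined on the complaint for which each patient was operated. Section 7.3 stratifies randomisation by indication.

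**The concern.** No single complaint is shared by all patients. Someone enrolled only for OSAS or dysphagia may never have had halitosis, detritus or tonsillitis. If that patient enters the halitosis comparison, the result is absence after surgery whichever procedure was done. The comparison then describes how common halitosis is in the operated population, not whether the procedure removed it in those who had it.

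Two things are at stake for these secondary outcomes. The reported absolute or mean difference is smaller than the difference among patients with something to cure. The test is also less likely to detect a real difference between the procedures. The arms stay comparable, so this is dilution and not bias between arms.

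**Working it through.** **Inputs from the protocol.** 95 patients per arm (7.4); two-sided 0.05 and Fisher's test (8.2). The only power stated is 80.2% for the primary log-rank test. It reproduces. The probability of recovery by day 14 is 1 − 2^(−14/8) = 0.703 and 1 − 2^(−14/13.5) = 0.513, giving 95 × (0.703 + 0.513) ≈ 115.5 events. The hazard ratio is 8/13.5 = 0.593, and the Schoenfeld formula gives 80.3%. This check serves only to confirm the sample size used below. No power or event rate is given for halitosis, detritus, tonsillitis or antibiotics.

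**Assumptions.** The protocol gives no baseline share affected (π), persistence or new-onset rate. I take persistence of 45% after laser and 10% after tonsillectomy among affected patients, new complaints in 0% or 5% of the others in both arms, and a range for π.

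**Absolute difference.** With new-onset rate q equal in both arms:

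rate in all patients = π × persistence + (1 − π) × q

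The q term cancels between arms, so the all-patient difference = π × (0.45 − 0.10) = 0.35π.

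- π = 30%: 0.35 × 0.30 = 10.5 points
- π = 40%: 0.35 × 0.40 = 14 points
- π = 60%: 0.35 × 0.60 = 21 points

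Among affected patients it is 35 points throughout.

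**Fisher power** (exact enumeration, fixed number affected per arm):

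| π | affected per arm | all patients, 5% new | all patients, no new | affected only |
|---|---|---|---|---|
| 30% | 28 | 53% | 72% | 79% |
| 40% | 38 | 77% | 88% | 92% |
| 60% | 57 | 97% | 98% | 99% |

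**A second scenario**, persistence 40% versus 10% with no new complaints, gives all-patient differences of 6, 12, 18 and 24 points at π = 20%, 40%, 60% and 80%, against 30 among affected patients. Power, all versus affected only, is 33% vs 46%, 77% vs 83%, 95% vs 96%, and 99% vs 99%.

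**Counts.** Assume Poisson means of 1.5 versus 0.9 episodes a year in half of the patients and none in the rest. The mean difference is 0.6 among those affected and 0.5 × 0.6 = 0.3 in all patients. Simulated power, all versus affected only, is 34% vs 73% for Mann-Whitney and 56% vs 77% for the t-test. The loss is largest for Mann-Whitney, because the added zeros become ties.

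**The case against.** The best reply is that the protocol never writes down a denominator for these endpoints. Intention-to-treat fixes the arm in which a patient is counted. A subset defined before randomisation and analysed as randomised is compatible with it, and an analysis plan that is not shown could name one. This stands: a reader might infer that 8.2 orders an all-patient comparison, but that is only the natural reading of endpoints listed without restriction next to a blanket rule. Nor does the protocol say that the baseline complaints will go unused; 8.1 says that the stored characteristics will be analysed.

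Whether the procedure cured what the patient came for is also already covered. The tonsil-related complaint is the first secondary endpoint, and 8.1 ties the effectiveness variable to the patient's own complaint. That outcome is not diluted.

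A reader might go further and infer that dilution would let laser pass the 30% limit in section 3. The documents do not support this. The limit concerns effectiveness in general, and nothing ties it to halitosis, detritus or tonsillitis counts.

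The size rests on assumed figures. Complaints overlap and secondary complaints are recorded, so the share with a complaint is at least the share enrolled for it, and at 60% to 80% the power gain nearly vanishes. A risk ratio is not diluted if unaffected patients stay at zero. Finally, the burden in all patients is a fair question, since laser leaves tonsil tissue behind; it should be reported, though separately.

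**Conclusion.** The point holds as a cheap improvement to a few secondary outcomes, not as an error that threatens the trial. On the natural reading of 5.2, 7.2 and 8.2, absolute and mean differences for halitosis, detritus, tonsillitis episodes and antibiotic courses shrink in proportion to the baseline share affected, provided new complaints are equally rare in both arms. That arithmetic does not depend on the assumed persistence. The power cost does: under 45% versus 10% with 5% new complaints it is 26 points at 30% affected (79 − 53), 15 at 40% (92 − 77) and 2 at 60% (99 − 97). In no scenario run was the restricted test the less powerful. The primary endpoint and the own-complaint outcome are unaffected. It would go too far to conclude that most patients had nothing to cure, or that laser would wrongly appear equivalent: the protocol gives no baseline prevalence and sets no equivalence limit for these endpoints.

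**What to change.** In 7.2 and 8.2, name the patients in each comparison:

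- Halitosis and detritus: compare the arms, as randomised, among patients with that complaint, main or other, on the baseline form.
- Tonsillitis episodes and antibiotic courses: compare among patients who reported tonsillitis, or antibiotic courses for it, at baseline. Do not restrict to the recurrent-tonsillitis indication. It requires more than four episodes a year, so it would drop patients with fewer episodes that could still improve.
- Report new complaints in the remaining patients, and the all-patient figures, separately.

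The subsets are fixed before randomisation, so the comparison remains randomised and by intention-to-treat.

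Cost: wording in two sections. Baseline complaints and past-year antibiotic use are already recorded. Section 8.1 lists no baseline count of tonsillitis episodes, so the rule must say which recorded items define tonsillitis at baseline. The downside is fewer patients in each complaint-specific comparison, for example 38 instead of 95 per arm at 40% affected.

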### 7.3. Randomization

After informed consent, the patient will be randomized to one of the two treatments. It is not possible to perform the study blinded. The drawing will be done by means of a stratification randomization, taking into account the indication. About 50% of the patient group will be randomized to a classic tonsillectomy and about 50% to a laser tonsillotomy.

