### 7.4. Sample size calculation

Using data from a previous non-randomized prospective study our group conducted a sample size calculation prior to conducting the present the randomized controlled trial. A two-sided log-rank test with an overall sample size of 190 subjects (95 in the TE group and 95 in the TO group) achieves 80.2% power at a 0.05 significance level to detect a TO median recovery time of 8 days when the TE group median survival time is 13.5 days within a 14-day total observation time.

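### Randomisation is stratified by indication, but no planned analysis is stated to use that factor; power is lost if indication predicts recovery

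*Protocol*

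**What the plan says.** Protocol section 7.3 describes allocation as "stratification randomization, taking into account the indication" and names no other factor. The ratio is roughly 1:1.

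Section 7.4 sizes the trial with this test: "A two-sided log-rank test with an overall sample size of 190 subjects". No strata are mentioned. The design "achieves 80.2% power at a 0.05 significance level", for median recovery of 8 days (laser) against 13.5 days (tonsillectomy) over 14 days of observation.

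Section 8.2 says of the primary outcome: "Survival analysis will be used to compare the primary outcome of recovery time". It names no test there. For secondary outcomes it names the unpaired t-test or Mann-Whitney test (continuous) and Fisher's exact test (proportions). It mentions neither indication nor centre.

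Section 5.2 lists five indications joined by and/or, so one patient can have several. Section 8.1 records a main complaint, but in six categories that do not map one-to-one onto those five.

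On setting, sections 4.1 and 6.1 place laser treatment at one hospital, with later expansion only by amendment. For the control arm, "The classic tonsillectomies will be performed in the operating rooms of the participating center where the patient has been enrolled".

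**The concern.** Stratified allocation balances the arms within each indication. If indication predicts the outcome, an analysis that ignores it counts the differences between indications as noise. The standard error is then too large for the design, and the overall hazard ratio lies nearer to 1 than the hazard ratio within indications. The planned power is only just above 80%, so even a modest prognostic effect would take an unstratified primary test below that level.

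For recovery time, the protocol does not say whether indication is prognostic. For several secondary endpoints in section 7.2 a link is plain: tonsillitis episodes, antibiotic courses for tonsillitis, halitosis and detritus must be expected to differ between a patient enrolled for recurrent tonsillitis and one enrolled for halitosis.

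**Working it through.** **Inputs from the protocol (7.3, 7.4).** 95 patients per arm, medians 8 and 13.5 days, 14 days of observation, two-sided 0.05, allocation about 1:1 within indication. **Assumed, because the protocol does not give them:** exponential recovery times, the sizes of the indication strata, and how strongly indication predicts recovery.

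**1. The plan's own figure.**
- Hazard ratio (tonsillectomy to laser) = 8/13.5 = 0.593; inverted, 13.5/8 = 1.69.
- P(recovered by day 14): laser 1 − 2^(−14/8) = 0.703; tonsillectomy 1 − 2^(−14/13.5) = 0.513.
- Expected events = 95 × (0.703 + 0.513) = 115.5.
- Schoenfeld power = Φ(√(115.5/4) × |ln 0.593| − 1.96) = Φ(2.81 − 1.96) = 80.3%, against 80.2% stated.

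The figure reproduces. Freedman's formula gives 78.5%.

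**2. Two equal indication strata.** Three sets of simulated trials, not identical in every modelling detail. Set A used 2000 trials per setting. Set B used 3000, with stratum hazards placed symmetrically about the plan's. Both rounded recovery to whole days; A censored at 14 days. Entries are power in %, unstratified / stratified log-rank.

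| Hazard ratio between strata | Set A | Set B | Set C |
|---|---|---|---|
| 1 | not tabulated | 80 / 80 | 77 / 77 |
| 2 | 78 / 80 | 77 / 81 | 77 / 80 |
| 3 | 75 / 81 | 69 / 80 | 69 / 79 |

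The level of power varies between sets, so read the gap within a set: 0 at ratio 1; 2, 4 and 3 points at ratio 2; 6, 11 and 10 points at ratio 3. Unrounded, set A at ratio 2 is 78.1 / 79.5, a gap of 1.4. With 2000 trials, the simulation error of one power figure is √(0.8 × 0.2/2000) = 0.9 points.

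**3. Other stratum layouts.** Strata of 70/30% and of 50/15/15/10/10%, 4000 trials per setting, recovery in continuous time. Prognostic strength is the SD of the log hazard between strata. For two equal strata with ratio R this SD is ln(R)/2, so R = 2 is 0.35 and R = 3 is 0.55.

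| SD of log hazard | Unstratified power | Stratified power | Unstratified type I error | Overall hazard ratio (1.69 within strata) |
|---|---|---|---|---|
| 0 | 80–81% | 79–81% | 5.1–5.4% | 1.68–1.70 |
| 0.2 | 78–80% | 78–81% | 4.7–4.9% | 1.67 |
| 0.4 | 73–75% | 79–80% | 4.1–4.7% | 1.62–1.63 |
| 0.6 | 67–69% | 78–80% | 3.1–3.6% | 1.56–1.57 |
| 0.8 | 54–58% | 77–78% | 2.0% | 1.48–1.50 |

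The loss is at most about 1 point at SD 0.2 and about 4 to 5 points at SD 0.4, where the hazards of the extreme indications differ by a factor of 2.4 to 3.2. It is larger only for stronger effects. Stratifying costs almost nothing when indication is irrelevant.

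**The case against.** **The primary test may already be meant to be stratified.** A reader might infer that the primary log-rank test is fixed as unstratified. The document does not go that far. The log-rank test appears only in 7.4, and a stratified log-rank test or Cox model fits the wording of 8.2. A statistical analysis plan, which is not shown, may specify one. This stands, and it limits the primary-outcome point to a link that is not stated. It does not cover the secondary outcomes, where 8.2 chooses named tests that cannot use strata.

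**The harm is conditional.** Section 7.3 gives no reason for stratifying, and indication may have been chosen with the complaint-based secondary outcomes in mind. If it does not predict recovery, nothing is lost. This stands.

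**Nothing is invalid.** A reader might infer that the 80.2% is wrong, that false positives are inflated, or that the estimate is biased. The figure reproduces, and simulated type I error is near 5% or below. The shift in hazard ratio is the difference between an overall and a within-indication quantity.

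**Centre.** A reader might infer that confining laser treatment to one hospital confounds the trial. Randomisation protects the comparison of the two treatments as delivered, setting included, and the share of patients enrolled elsewhere is not given. For those patients hospital does differ by arm, so the effect of technique alone is not isolated. Adjusting for enrolling centre would not isolate it either.

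**Rare events.** Stratified methods for every proportion would be a poor choice. At the Summary's bleeding rates (below 1% for laser, about 1.4% for tonsillectomy), 95 patients yield fewer than 0.95 and about 1.3 events (95 × 0.01; 95 × 0.014). Fisher's exact test is defensible there.

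**Conclusion.** The point holds as a gap between design and analysis: indication governs allocation, and no analysis is stated to use it. The consequence is possible inefficiency. The planned tests are valid and, where indication is prognostic, conservative. The sample size need not change on the protocol's own figures.

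For the primary outcome, the loss from an unstratified test runs from nothing to about 2 to 4 points at a stratum hazard ratio of 2 and about 6 to 11 points at 3. This assumes exponential times, two equal strata and the plan's medians. The protocol cannot say where in this range the trial lies. The centre question is secondary and does not undermine the randomised comparison.

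**What to change.** In section 8.2:

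- Make the primary test a log-rank test stratified by the indication used at randomisation, with a Cox model stratified the same way for the hazard ratio.
- Use one main indication per patient, as recorded at randomisation, because the indications in 5.2 can overlap. Pool sparse indications by a rule fixed before analysis.
- For continuous and common binary secondary outcomes, adjust or stratify for indication. Keep Fisher's exact test for rare complications.
- Optionally, add a supportive sensitivity analysis of the primary endpoint in patients enrolled at the laser hospital. It removes the difference between hospitals, but it has lower power and leaves operator differences in place.

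The cost is wording only, with no new patients or data. Small strata may need pooling, and the loss is negligible if indication proves not to be prognostic.
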